#### NMM

For the NMM study, each participant will complete the screening questionnaire to determine study eligibility, followed by a baseline survey, a midline survey (prior to birth of child), and an endline survey. Survey domains will include intent to vaccinate self and child, vaccine confidence (Emory Vaccine Confidence Index [26]), health information seeking patterns, and demographics. Midline and endline surveys will evaluate acceptability of the adaptive components of the intervention. Prior to the surveys, each participant will complete an informed consent form, which will describe study processes, risks and benefits. Qualitative data will be collected using open-ended questions and prompts in individual in-depth interviews from participants who completed the endline surveys. Interview question domains may include reasons for delayed or timely vaccinations, feedback on intervention components, and residual information needs. Interviews will be held in English, over the phone or in person and are expected to last approximately 30 minutes each. The interview guide themes and questions will be influenced by the quantitative outcomes and used to benefit from further exploration. Interviews will be audio recorded to facilitate data transcription and analysis.

### Statistical considerations

#### Sample sizes

*Provider trainings*. Only individuals from the intervention practices will be offered access to the trainings. All providers, staff and trainees at these practices will be eligible to participate in the training.

*CRT*. We anticipate the proportion of children who receive delayed or no vaccination at 2 months of age at baseline to be 20% [6]. We estimate that the intervention will reduce this proportion to 10%. We used a sample size formula for a two-sided Z-test comparing two proportions that accounts for the CRT design and incorporates a small-sample bias correction suitable for CRTs with fewer than 30–40 clusters in total (see equation (3) of Thomson et al, and more details in **S5 File**) [27]. With a sample size of 7 practices in each arm (14 total) and with at least 55 PIs/practice (770 total) the study would be powered at 90% to detect a difference in the proportion of 10% between arms at a two-sided alpha level of 5%, assuming that the coefficient of variation of cluster (i.e., practice-level) proportions with the primary outcome is 0.15 [27]. The target sample size is further inflated by 10% (total: 850) to accommodate a small reduction in power anticipated due to variable enrollment by practice and a small proportion of children with missing effectiveness outcomes due to out-of-state movement [28, 29]. In reality, the sample size for each practice will depend on practice size and eligibility of the PI population seen during the study period. Given that the primary outcome will be measured via data linkage of practice-level data to the state immunization registry using an honest broker, we will request an extract of data for all eligible PIs who are seen at the practice during the study period with the goal that the majority of enrolled practices would be expected to meet this target. Sensitivity analyses show that 80% power would be achieved if the proportion of children who delayed or refused vaccination at 2 months of age is 30% (rather than 20%) with a slightly smaller CV of 0.125 or even if the coefficient of variation is as large as 0.2 (**S5 File**).

*NMM*. Sample size for the quantitative surveys will be estimated with the assumption that 20% of 425 PIs in the intervention arm are vaccine hesitant, and, hence, 85 PIs will be eligible to receive the adaptive intervention components as part of the NMM study. Of these, 68 are expected to agree to participate and to have midline survey data available (accounting for loss to follow-up) and estimate that the intervention will reduce the proportion of vaccine-hesitant to 80% at that time point. Using exact binomial methods, data from 68 PIs in a non-clustered setting would provide a 95% confidence interval ranging from 68% to 89% for a proportion vaccine-hesitant of 80% with a small increase due to the small design effect anticipated due to clustering. For the qualitative portion, existing research suggests that thematic saturation can be achieved with 12 interviews, with meta-themes presenting as early as six interviews [30, 31]. The proposed sample size of 24 PIs should be sufficient to achieve thematic saturation of reasons for delayed/refused vaccinations (n = 12) or timely vaccinations (n = 12).

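### The 80% power stated for a 30% baseline with CV 0.125 comes out at about 74% under the corrected formula that reproduces the plan's own 90% figure, if the 10-point difference and 55 per practice carry over

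*Protocol article*

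**What the plan says.** All of this is in the protocol article, Statistical considerations, Sample sizes, paragraph on the cluster-randomized trial.

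- Baseline rate of delayed or no vaccination: "We anticipate the proportion of children who receive delayed or no vaccination at 2 months of age at baseline to be 20" per cent. Effect: "We estimate that the intervention will reduce this proportion to 10" per cent.
- Method: a two-sided Z-test for two proportions in a cluster trial that "incorporates a small-sample bias correction suitable for CRTs with fewer than 30–40 clusters in total". The equation is cited, and details are deferred to S5 File.
- Main result: "With a sample size of 7 practices in each arm (14 total) and with at least 55 PIs/practice (770 total"), the study is "powered at 90% to detect a difference in the proportion of 10% between arms at a two-sided alpha level of 5" per cent, at a CV of 0.15.
- The target is then raised by 10% to 850, to cover unequal enrolment across practices and children with missing outcomes.
- Sensitivity: "80% power would be achieved if the proportion of children who delayed or refused vaccination at 2 months of age is 30" per cent ("rather than 20%) with a slightly smaller CV of 0.125 or even if the coefficient of variation is as large as 0.2"), again with reference to S5 File.

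For the 30% case the sentence gives a baseline and a CV. It does not restate the intervention-arm proportion, the number per practice or the number of practices, and nothing suggests that the correction was switched off.

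**The concern.** The main and sensitivity figures stand in one paragraph under one described method, so the same formula should give both. Moving from 20% vs 10% to 30% vs 20% keeps the difference at 10 points but raises the binomial variance by nearly half (0.25 to 0.37, before division by cluster size). The between-practice term also rises, despite the smaller CV, because it scales with the squared proportions. A drop from 90% to only 80% looked small for that change.

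This sentence is the article's only stated check that the trial tolerates a less favourable baseline. If it is optimistic by five or six points, the chance of missing a true 10-point effect in that case is about one in four (25.5%) rather than one in five.

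**Working it through.** **Inputs from the article:** two-sided alpha 5% (z = 1.96); c = 7 practices per arm; m = 55 PIs per practice; main case p0 = 0.20, p1 = 0.10, CV k = 0.15; sensitivity case p0 = 0.30, k = 0.125.

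**Assumptions:** for the 30% case, p1 = 0.20 (the stated 10-point difference), c = 7 and m = 55 carry over. The cited equation is not shown, so the form of the correction is inferred from the main figure.

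**Formula**

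V = [p0(1−p0) + p1(1−p1)]/m + k²(p0² + p1²)

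Power with correction = Φ( |p0−p1| / √(V/(c−1)) − 1.96 )

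Power without correction: the same with c in place of c−1.

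**Step 1. Reproduce the main figure (20% vs 10%, k = 0.15, m = 55)**

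V = (0.16 + 0.09)/55 + 0.0225 × (0.04 + 0.01) = 0.004545 + 0.001125 = 0.005670

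- Corrected: √(V/6) = 0.03074; 0.10/0.03074 = 3.253; Φ(1.293) = **90.2%**. Practices needed per arm for 90%: 1 + 5.958 = 6.96, so 7. The m needed with 7 per arm is 54.5, so 55.
- Uncorrected: √(V/7) = 0.02846; Φ(1.554) = 94.0%. Only about 45 per practice would be needed.

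The corrected form returns the printed 90%, 7 and 55. The uncorrected form does not.

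**Step 2. The 30% case (30% vs 20%, k = 0.125, m = 55)**

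V = (0.21 + 0.16)/55 + 0.015625 × (0.09 + 0.04) = 0.006727 + 0.002031 = 0.008758

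- Corrected: √(V/6) = 0.03821; 0.10/0.03821 = 2.617; Φ(0.657) = **74.5%**.
- Uncorrected: √(V/7) = 0.03537; 0.10/0.03537 = 2.827; Φ(0.867) = **80.7%**.

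**Step 3. Does the form of the correction matter?** Replacing the lost cluster by t-based corrections on 12 degrees of freedom (central t, noncentral t, or normal with a t critical value) gives 89.6% to 90.9% in the main case and 73.5% to 74.2% in the 30% case. The shortfall does not depend on the one-cluster form.

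**Step 4. CV 0.2 at 20% vs 10%.** V = 0.004545 + 0.04 × 0.05 = 0.006545; 0.10/√(V/6) = 3.028; Φ(1.068) = **85.7%**. That part of the sentence holds, read as at least 80%.

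**Step 5. What would give 80% at a 30% baseline with the correction kept?**

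| Change from Step 2 | Corrected power |
|---|---|
| m = 60.7 (850/14) | 77.6% |
| m = 61 | 77.7% |
| m = 66 (924 total) | 80.0% |
| 8 practices per arm | 80.7% |
| p1 = 21% | 64.5% |
| p1 = 19% | 82.8% |
| p1 = 15% (halving) | 98.5% |

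At m = 55, 80% is reached at about p1 = 19.3%, or at 30% vs 20% with a CV of at most about 0.084. The article states none of the inputs that reach 80%.

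**The case against.** The strongest reply is that the disputed scenario is not fully specified in print. The intervention proportion and cluster size for the 30% case have to be carried over, and the correction is calibrated on a single figure. That stands, and it makes the 74% conditional. It does not remove the problem, because the sentence presents only the baseline and the CV as changing.

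A second reply is that the planned effect is also a halving, so 30% might mean 30% vs 15%. Power would then be 98.5%, so that at least 80% is technically true. But with power that high there would be no reason to pair the scenario with a smaller CV or to describe it as 80%. The main claim is itself framed as a 10-point difference.

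A third reply is that 55 is a floor and the target is 850. At about 61 per practice the gap narrows to some two points. That gives partial relief only, since the article reserves the extra 10% for unequal enrolment and missing outcomes.

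Three stronger readings are tempting, and the article does not support them:

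- **That the correction was certainly dropped.** The 80.7% match makes this likely. However, 80% can also arise with the correction kept, for instance at 66 per practice or with a difference of about 10.7 points. Without S5 the cause is an inference.
- **That CV 0.2 is also wrong.** At 30% vs 20% with CV 0.2, power would be 61%. But the clause reads more naturally as a separate scenario at the 20% baseline, where it holds.
- **That the investigators' own survey shows a 30% baseline is likely.** The 67% in the Background is prenatal intention to accept all vaccines at practices of one academic center. It is not a rate of delayed or missed 2-month doses, and is weak evidence for a 30% delay rate.

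**Conclusion.** The concern holds in conditional form. With 30% vs 20%, CV 0.125, 7 practices per arm and 55 per practice, the method that reproduces the article's 90% gives about 74%, not 80%: a shortfall of 5.5 points in the optimistic direction.

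The conclusion rests on the carried-over difference, number of practices and cluster size, and on a correction inferred from the main figure. The t-based check makes the last of these a minor dependence. The intervention proportion matters most: one point either side of 20% moves power between 64.5% and 82.8%.

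The error is confined to one sensitivity statement. It gives no ground for doubting the 90% power, the total of 770 or the planned analysis.

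**What to change.** Restate the sensitivity sentence with its inputs: power is about 74% for 30% vs 20%, CV 0.125 and 55 PIs per practice (about 78% at 61 per practice, before any loss to unequal enrolment or missing outcomes), and about 86% for 20% vs 10%, CV 0.2 and 55 per practice. Naming the baseline beside the CV of 0.2 also removes the ambiguity in that clause.

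Check S5 File against these figures. If it used a different intervention proportion, a different cluster size or no correction for the 30% case, print those inputs beside the power figure, so that the reader can see it is not on the same footing as the 90%.

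The cost is wording and a recheck of one supplementary calculation. The design, sample size and analysis do not change; one stated figure becomes less favourable.

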### Randomization

An independent biostatistician at the study institution will generate the randomization sequence. Practices will be allocated using a 1:1 ratio to the intervention or control arm. A covariate constrained randomized approach will be implemented in order to facilitate comparability between arms in practice-level characteristics [32]. Practices will first be stratified by type (e.g., based on their affiliation with the academic medical center or the health department). Within strata, the following covariates will be considered: Practice size (quantified as # providers or patient volume), Race/ethnicity of the PI (African American vs not, Latinx vs. not i.e. two variables), and Insurance type of the PI. The choice of the race/ethnicity variable is based on our prior findings suggesting higher hesitancy among self-identified Black or African American pregnant individuals [9]. Final covariate selection will depend on data quality and completeness. There is no randomization of participants in the NMM study.

### Outcomes

The primary study outcome is the proportion of children receiving timely vaccinations at 2 months post birth, by study arm. The secondary outcome is change in vaccine hesitancy among PIs who receive the adaptive components of the intervention, within the intervention arm only, where change is measured from baseline to midline of the NMM (i.e., before and after receiving ADEPT intervention).

### Data analysis

All analyses of quantitative outcomes will utilize analytic software, such as SAS or STATA, and qualitative analyses will be conducted utilizing software such as MaxQDA.

#### Provider training

Summary characteristics for consenting providers will be described by study practice. Summary statistics will be calculated from data on provider training. Broad thematic domains from interviews with providers will be identified and cross referenced with quantitative data.

#### CRT

Summary characteristics for study practices will be described by intervention and control arm. We will also describe the distribution of vaccination intention among PIs. A timeframe of 28 days from the vaccination due date will be used as the window of timeliness. Timely vaccination doses will receive a score of 2, doses that are delayed beyond the 28-day window will receive a score of 1, and the non-receipt of a dose during outcome assessment will be scored a 0. For the time point of outcome determination (2 months), we will create a cumulative timeliness score and use that to determine the proportion of children who receive all recommended vaccines in a timely fashion. For the analysis of the primary outcome of vaccination timeliness, we will use data on vaccination outcomes for children of all PIs enrolled in the study (including those who screened as vaccine-hesitant in the intervention arm). The generalized estimating equations (GEE) approach will be used to account for clustering of outcomes due to the hierarchical structure of data (PIs nested within practice). The child-level binary outcome (timely vs. not) will be regressed on an intervention-arm indicator, strata and the practice-level covariates used in the covariate constrained randomization procedure. We note that no additional adjustment by individual-level characteristics is possible due to the source of data, i.e., state immunization registry. Log and identity links will be used to obtain both relative and absolute intervention effects, as per recommendations from the CONSORT statement on trial reporting [22]. Robust standard errors will be used together with finite-sample corrections to reduce inflated Type I error rate, which is expected due to the small numbers of clusters (I.e. 14 practices) [33]. Given that outcomes are obtained from the state immunization registry, we do not expect missing data in the usual sense. Instead, some outcome data will not be available for those children whose birthing parents were enrolled towards the end of the study. Since this is by design, the missing data is not expected to bias the estimated intervention effect. A similar GEE approach will be used to model vaccination coverage.

#### NMM

Summary characteristics of PIs enrolled and receiving the adaptive components of the intervention will be computed. The secondary outcome of the study, change in vaccine hesitancy from baseline to midline, will be computed utilizing data collected from enrolled PIs prior to receipt of the intervention, and at midline (up to 2 months post intervention, prior to birth). Given the anticipated sample size of PIs enrolled in the NMM study, we anticipate being underpowered to detect any meaningful pre-post difference. However, the determination of this outcome is important to inform sample size estimates for future studies.

Thematic analysis of qualitative data will occur using a phenomenological lens using the following steps: A) an initial read through of the transcripts to evaluate content and quality, b) coding of a priori themes based on the interview guide during a second read through and an additional review of 10% sample coded transcripts by a secondary team member, c) display of data through patterns and subthemes/codes and descriptions in thematic memos, and D) data reduction by applying matrices to organize and extract the key concepts on vaccine hesitancy.

Mixed methods data integration will occur using a joint display. Qualitative themes explaining the vaccination decision and describing residual barriers will be organized by a joint display by quantitative outcomes as follows: ADEPT and timely vaccinations, ADEPT, and delayed vaccinations. The joint display will be used to facilitate an explanation of the impact of ADEPT on timely vaccination [24].

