**Methods:**

Within the framework of a type 1 effectiveness-implementation hybrid study design, a cluster-randomized trial (CRT) will determine the effectiveness of ADEPT at increasing childhood vaccinations, and a nested explanatory mixed methods (NMM) study will assess changes in parental vaccine hesitancy. Study practices will be randomized to deliver ADEPT in addition to standard of care or standard of care alone. Providers at intervention sites will participate in a 4-part training program on childhood vaccines and effective communication. During a routine prenatal visit, providers will discuss vaccines recommended for the PI during pregnancy and for the child after birth, following which PIs will be screened for vaccination intention. Vaccine-hesitant PIs will be offered adaptive components of the intervention, which include an educational website and phone call with a vaccine navigator to discuss concerns. They will also be offered enrollment into the NMM study, where their vaccination intention will be assessed post-intervention. After PIs give birth, their child’s vaccination outcomes at 2 months will be extracted from the state immunization registry. The primary study outcome is the difference in timely childhood vaccination at 2 months between the intervention and control arms. The secondary outcome is reduction in vaccine hesitancy assessed among PIs in the NMM study as the pre-post intervention change in vaccination intention.

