### Description of the intervention

The ADEPT intervention components are described in accordance with the template for intervention description and replication (TiDieR) checklist (**S2 File**) [20]. The core and adaptive components of ADEPT are shown in **Fig 2**. The core component of ADEPT is a prenatal provider recommendation in favor of maternal and childhood vaccinations. Adaptive components include a multimedia educational website and phone consultations with a vaccine navigator. These components are described below.

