#### Adaptive components

The ADEPT intervention consists of two adaptive components: a multimedia vaccine education website and phone consultations with a vaccine navigator. The assignment of the adaptive component is determined based on a screening questionnaire that will assess vaccination intention, that is administered after the core component is delivered to the PI. PIs who have a positive vaccination intention will not receive any adaptive intervention components. PIs who are in favor of vaccinations but exhibit some degree of hesitancy (e.g., plan to delay some vaccines) will be offered access to the multimedia vaccine education website. PIs with negative intention to vaccinate or those unsure of their decision will be offered access to the multimedia vaccine education website, as well as a phone consultation with a vaccine navigator.

Multimedia vaccine education website: An educational website was co-developed with parents. The website includes the following sections: About Us, About Vaccines, Vaccine Preventable Diseases, About the Schedule, Vaccination Schedule, Vaccines During Pregnancy, Visit Detail, What Doctors Say, Research with Confidence, Vaccines by Numbers, and More Resources. The ‘More Resources’ tab includes links to other credible websites such as cdc.gov and the American Academy of Pediatrics’ Healthy Children webpage for those interested in learning more. PIs without sufficient access to the internet or an internet-enabled device, may request access to a handout with the website content. Such individuals will also be reassigned automatically to receive a phone consultation with a vaccine navigator.Vaccine Navigator: The navigators are members of the study team and will connect with eligible PIs via phone. The vaccine navigators will participate in the provider trainings described with the core component of the intervention. The purpose of the navigator is to respond to questions or concerns not addressed by the website or during provider recommendation.

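### The secondary outcome is labelled a before/after-ADEPT change, but its baseline follows the core component and is taken only in PIs who still screen hesitant

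*Protocol article*

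**What the plan says.** All references are to the protocol article.

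- **Outcomes** restricts the secondary outcome to intervention-arm PIs who receive the adaptive components, "where change is measured from baseline to midline of the NMM (i.e., before and after receiving ADEPT intervention").
- **Data analysis (NMM)** says the change "will be computed utilizing data collected from enrolled PIs prior to receipt of the intervention", and at midline. The Abstract likewise calls it a pre-post intervention change in vaccination intention.
- **Description of the intervention** makes the recommendation part of ADEPT: "The core component of ADEPT is a prenatal provider recommendation in favor of maternal and childhood vaccinations".
- **Adaptive components** describes a screening questionnaire "that is administered after the core component is delivered to the PI". The Abstract gives the same order: providers discuss vaccines, "following which PIs will be screened for vaccination intention".
- **Recruitment (PIs)** limits NMM recruitment to intervention-arm PIs who are hesitant on that questionnaire.
- **Data collection (NMM)** gives the order of measurement: "each participant will complete the screening questionnaire to determine study eligibility, followed by a baseline survey, a midline survey (prior to birth of child"), then an endline survey.
- **Sample sizes (NMM)** starts from 85 hesitant PIs, expects 68 with midline data, and the authors "estimate that the intervention will reduce the proportion of vaccine-hesitant to 80% at that time point".

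**The concern.** The label and the sequence of measurements do not agree. By the time of the NMM baseline every participant should already have had the core component, so nothing measured there is before ADEPT. Two consequences follow.

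1. **The core effect is missing.** PIs whom the recommendation persuaded screen as non-hesitant and never enter. Any partial shift in those who remain has happened before baseline.
2. **Entry depends on the outcome.** Participants are chosen because they scored as hesitant, and no hesitancy measure is described in the control arm. Some will score as less hesitant when asked again, whatever they receive. The sample-size text nevertheless credits the whole expected fall to the intervention.

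The two distortions can pull in opposite directions: the first may understate what ADEPT does, and the second may overstate it. The reported change would then be neither an effect of ADEPT nor a clean effect of its adaptive part. The protocol also intends the result to inform the size of future studies, so the ambiguity would carry forward.

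**Working it through.** **Step 1: order of events**

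| Step | Event | Section |
|---|---|---|
| 1 | Core component: provider recommendation | Description of the intervention; Core component |
| 2 | Screening questionnaire | Abstract; Adaptive components |
| 3 | Adaptive components offered, and NMM recruitment, in those who screen hesitant | Adaptive components; Recruitment (PIs) |
| 4 | Consent, then baseline survey | Data collection (NMM) |
| 5 | Midline survey, before birth | Data collection (NMM) |

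A baseline at step 4 cannot be before ADEPT if ADEPT begins at step 1. It can be before the adaptive components, provided that website or navigator access comes after the survey. Only the general phrase in Data analysis (NMM) bears on that order.

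**Step 2: the plan's own figures**

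- Eligible: 0.20 × 425 = 85. Expected with midline data: 68, and 68/85 = 0.80.
- Still hesitant at midline: 0.80 × 68 = 54.4.
- Exact 95% interval: lower limit is the 2.5% quantile of Beta(x, n − x + 1); upper limit is the 97.5% quantile of Beta(x + 1, n − x); n = 68.

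| x | Lower | Upper |
|---|---|---|
| 54 | 67.9% | 88.3% |
| 54.4 | 68.5% | 88.7% |
| 55 | 69.5% | 89.4% |

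The stated 68% to 89% is reproduced to within rounding. The arithmetic is sound; the question is what the change means.

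**Step 3: the implied start**

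All 85 are counted because they are hesitant, so the sizing implies 100% at entry and a fall of 100 − 80 = 20 percentage points.

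**Step 4: could re-measurement alone produce a fall of that size?**

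The document gives no re-test reliability, so the values below are assumptions. Both models take 20% as screening hesitant, assume no intervention effect, and use the qualifying screen as the starting point, as the sizing does.

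*Continuous intention score.* The two scores are bivariate normal with correlation r, and hesitant means beyond the cut-off for the extreme 20%. Share still hesitant = P(beyond the cut-off both times) / 0.20.

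| Assumed r | Still hesitant |
|---|---|
| 0.99 | 92% |
| 0.95 | 82% |
| 0.90 | 75% |
| 0.80 | 65% |
| 0.70 | 57% |

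*Yes/no classification with independent errors.* With sensitivity se and specificity sp, the true prevalence is π = (0.20 − (1 − sp)) / (se + sp − 1). Then PPV = π × se / 0.20, and the share still hesitant is PPV × se + (1 − PPV)(1 − sp). For se = 0.90 and sp = 0.97: π = 0.17/0.87 = 0.195, PPV = 0.879, and the share is 0.791 + 0.004 = 0.795. Other pairs give 88% (0.95/0.98), 73% (0.90/0.95) and 69% (0.85/0.95).

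The planned 80% lies inside both ranges. This shows that the artefact can be as large as the planned effect. It does not estimate how large it will be.

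**The case against.** The strongest reply is that the protocol already narrows the outcome. Outcomes restricts it to recipients of the adaptive components in the intervention arm, so the intervention in Data analysis (NMM) may mean only those components. On that reading the baseline is before them, as it should be, and the error is one of wording. Much of this stands: the restricted population is disclosed. But the parenthesis in Outcomes names ADEPT, and the narrow reading does not remove selection on the outcome or supply a comparator. The limitations mention self-selection into enrolment and low power, but neither the post-core baseline nor regression to the mean.

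Three stronger readings are tempting, and the document does not support them.

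- **That measured change can only go down from 100%.** The plan takes change from a separate baseline survey that asks about intent, and intention is graded. A participant can score differently there than on the screen, and can worsen. The 100% start is implied only by the sizing text. If the baseline survey is the pre value, part of the regression will already have occurred.
- **That a spurious significant reduction is likely.** No hypothesis test is stated for this outcome; it is sized by interval width. Any false-positive rate would need an unplanned test, a fixed 100% start and invented re-test rates.
- **That the sizing contradicts the statement "we anticipate being underpowered to detect any meaningful pre-post difference".** An interval that excludes 100% proves little, because an exact upper limit falls below 100% once a single participant is reclassified (67 of 68 gives about 99.96%). It says nothing about power for a paired change.

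Nor does the text show that adaptive access will come before the baseline survey. The schedule figure is not shown, and reading the phrase as before the adaptive components is the only coherent one. It should simply be stated.

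**Conclusion.** The point holds in limited form. The before-and-after-ADEPT label contradicts the protocol's own sequence, and this rests on the text alone. The outcome leaves out any core effect and describes only PIs still hesitant after the core. As an uncontrolled change in a group selected on hesitancy, it cannot separate an effect of the adaptive components from regression to the mean. How much of the planned 20-point fall could be artefact is unknown. Under the assumed reliabilities it ranges from 100 − 92 = 8 points to 100 − 57 = 43 points when the screen is the starting point, and should be smaller when the baseline survey is.

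This is a should-fix point on the only named secondary outcome. A reader might infer that the trial cannot assess ADEPT as a whole. It can: the randomised comparison of timely vaccination covers core and adaptive components together and is untouched.

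**What to change.** 1. In the Abstract, Outcomes and Data analysis (NMM), redefine the secondary outcome as change from the post-consent baseline survey to midline, after the adaptive components, among intervention-arm PIs still hesitant after the core recommendation.
2. State that the baseline precedes website or navigator access, and that the baseline survey, not the qualifying screen, supplies the pre value.
3. Bring Sample sizes (NMM) into line: drop the implied 100% start and do not credit the whole fall to the intervention.
4. Report screen-to-baseline change in intention as a gauge of regression to the mean. It is only a gauge, since a delayed core effect could contribute to it and it needs a comparable intention item on both instruments.
5. List regression to the mean and the missing comparator as limitations, and do not attribute the change to ADEPT as a whole.

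The cost is wording, one ordering statement and one extra tabulation of data already planned for collection. The price is a narrower, descriptive claim.
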